### Coagulopathy

Coagulopathy does not affect the choice of catheterisation site and is thus of no importance with regard to study participation. Procoagulants can be administered at the discretion of the operator.

### Catheterisation protocol

Catheterisations will be performed in a standardised manner. A post-procedural chest x-ray is performed in every patient. Acceptable catheter tip locations are in the upper right atrium, at the cavo-atrial junction or in the superior vena cava with the catheter aligned with the vessel.

### Criteria for discontinuing or modifying allocated interventions {11b}

As the data will be analysed on a per protocol basis, patients that do not complete the follow-up for a specific outcome will not be included in the analyses of that outcome.

### Reasons to exit the trial

Inability to place the catheter in the randomised vein for any reason (the catheter may then be placed in any vein at the discretion of the operator)Inability to achieve a correct catheter tip locationPatient desires to no longer take part in the trial

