#### Objectives

To determine if the incidence of post-catheterisation CVS detected by a CT venography performed 1.5–3 months after removal of the tCDC is non-inferior when the right subclavian route is used as compared to the right internal jugular routeTo compare the performance of a focused ultrasound examination of the central veins to detect CVS with a CT venography (golden standard) with a threshold ofa50% venous diameter/area reduction (corresponding to moderate CVS in this study), as this is the commonly used definition of CVS [11]b80% venous diameter/area reduction (corresponding to severe CVS in this study), as it has been suggested that the severity of central veno-occlusive disease must reach a diameter reduction around 80% before upstream changes in blood flow are detectable by current Doppler techniques [12]To compare the patients’ experience of discomfort and pain between the groupsaDuring the catheterisation, using a questionnaire (Additional file 1) handed out immediately after insertionbWhen carrying the catheter, using a questionnaire (Additional file 2) handed out as soon as possible after catheter removalTo compare the function of the tCDC during dialysis or plasmapheresis between the groups, using a questionnaire filled out by the dialysis nurse after each treatment session. The questionnaire (Additional file 3) includes both objective and subjective parametersTo compare the catheterisation success rate (defined as catheter tip placement in the right atrium or in the superior vena cava with the catheter aligned with the vessel) between the two groups using a post-procedural chest x-rayTo compare the number of mechanical complications (defined as arterial puncture/catheterisation and pneumothorax) between the groups

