### Reasons for exclusion from primary outcome analyses as well as the secondary outcome concerning ultrasound examination

The patient is unable to perform a follow-up CT venography. Reasons for this include, but is not limited toaAn estimated glomerular filtration rate < 15 ml/min without ongoing dialysis treatment at the time for the CT scanbThe patient dies before follow-upThe tCDC is in situ for < 7 daysAn additional central venous catheter is placed in the right-sided subclavian or internal jugular vein before the follow-up CT. Vein punctures without catheterisation are accepted (e.g. for myocardial biopsies after heart transplant surgery)

Reasons for exit from the trial and for exclusion in any of the analyses will be collected and reported. Data from the questionnaire about discomfort and pain during the catheterisation procedure will be used regardless and the questionnaire about discomfort and pain during the use of the tCDC will be used if the tCDC has been in situ for ≥ 7 days.

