### Outcomes {12}

The primary outcome is the incidence of post-catheterisation CVS, defined as venous diameter reduction > 50% anywhere from the estimated insertion site to the tip of the catheter, detected by a CT venography performed 1.5–3 months after removal of the tCDC.

The CT venography will be performed according to a protocol designed for this trial (Attachment 1) with the purpose to keep the amount of intravenous contrast and radiation as low as possible (with a limit of 100 kV the amount of intravenous contrast is reduced by 30% and less radiation is needed by repositioning the shoulders in an arm holder).

The secondary outcomes are:To compare the performance of a focused ultrasound examination of the central veins to detect CVS with a CT venography (golden standard) with a threshold ofa50% venous diameter reduction, as this is the commonly used definition of CVSb80% venous diameter reduction, as it has been suggested that the severity of central veno-occlusive disease must reach a diameter reduction around 80% before upstream changes in blood flow are detectable by current Doppler techniquesTo compare the patients’ experience of discomfort and pain between the groups both during the catheterisation and when carrying the catheter by means of a questionnaire (Additional files 1 and 2)To compare catheter blood flow during dialysis and reported catheter-related dialysis dysfunction between the groups. A questionnaire to address this will be filled out by the dialysis nurse after every treatment, including both objective and subjective measures (Additional file 3)To compare the catheterisation success rate (defined as catheter tip placement in the superior vena cava or in the right atrium) between the two groupsTo compare the number of mechanical complications (defined as arterial puncture/catheterisation and pneumothorax) between the groups

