## Statistical methods

### Statistical methods for primary and secondary outcomes {20a}

The study aims to explore if the incidence of post-catheterisation CVS when using the right-sided subclavian route is non-inferior to the internal jugular route. All patients randomised in this trial will be analysed on a per-protocol basis. The primary outcome will thus be analysed only in patients subjected to the follow-up CT venography. Patients will be enrolled using previous exit rates to determine when the calculated sample size for both groups can be reached.

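### The trial-exit rules are the failure events of the success-rate outcome, and the protocol's own rules conflict on whether exited patients count for success rate and mechanical complications

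*Protocol article*

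**What the plan says.** All references are to the protocol article.

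- **Reasons to exit the trial** names "Inability to place the catheter in the randomised vein for any reason", then failure to reach a correct tip location, then the patient's wish to stop.
- **Outcomes {12}** includes, as a between-group secondary outcome, "To compare the catheterisation success rate (defined as catheter tip placement in the superior vena cava or in the right atrium". It also includes mechanical complications, meaning arterial puncture or catheterisation and pneumothorax.
- **Statistical methods {20a}** states: "All patients randomised in this trial will be analysed on a per-protocol basis". The sentence after it spells out the consequence for the primary outcome only.
- **Section {11b}** states: "patients that do not complete the follow-up for a specific outcome will not be included in the analyses of that outcome".
- **Reasons for exclusion from primary outcome analyses** (headed for the CT and ultrasound outcomes) states: "Data from the questionnaire about discomfort and pain during the catheterisation procedure will be used regardless". The questionnaire on carrying the catheter "will be used if the tCDC has been in situ for" 7 days or longer. No matching sentence covers success rate or mechanical complications.
- **Tip location** is worded three ways. Objectives {7} has "right atrium or in the superior vena cava with the catheter aligned with the vessel". Outcomes {12} has no alignment condition. The Catheterisation protocol has "Acceptable catheter tip locations are in the upper right atrium, at the cavo-atrial junction or in the superior vena cava", with alignment required for the last.

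**The concern.** An outcome should not decide who is analysed for it. Here, failing to place the catheter or to position its tip is both the event of interest and a reason to leave the trial. If leaving also means leaving the analysis, the success comparison has little or nothing left to compare, and a pneumothorax or arterial puncture during an abandoned attempt goes uncounted.

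These are the two secondary comparisons that concern the insertion itself, and the Background cites more misplacements for the right subclavian than for the right jugular route. A rule that removes failures would push the success comparison towards no difference, in favour of the experimental route. Two analysts could each follow the text faithfully and report opposite results.

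**Working it through.** **1. The plan's own figure.** Inputs from Sample size {14}: 10% event rate (taken as equal in both arms), 15-point margin, one-sided 5%, 80% power.

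n per group = [0.10 × 0.90 + 0.10 × 0.90] × (1.6449 + 0.8416)² / 0.15² = 0.18 × 6.1827 / 0.0225 = 49.46, rounded up to 50.

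The stated 50 per group reproduces and is not affected by this point. The same section expects at least 200 inclusions, so about 100 per arm.

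**2. The two readings side by side.**

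| | Literal reading | Outcome-specific reading |
|---|---|---|
| Rests on | Exit list with {20a} | {11b} |
| Failed placement or wrong tip | Outside the per-protocol set | Result known at insertion or on the chest x-ray done in all patients, so counted |
| Success rate | Computed among successes | Failures in the denominator |
| Complications of failed attempts | Lost | Counted |

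No sentence says that exited patients are dropped from these two outcomes, and none says that they are kept. Section {20b} does not settle it: its list of other secondary outcomes leaves out success rate and gives no analysis set for complications. Retention section {18b} sends the reader to {11b} for outcomes that may still be collected in patients without complete follow-up. The only such outcomes named under that section and its subsections are the two questionnaires.

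**3. Size for success rate.** Assumption: the Background misplacement rates act as failure rates, with 100 per arm.

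- Expected failures: 100 × 0.014 = 1.4 jugular; 100 × 0.091 = 9.1 subclavian.
- All attempted insertions kept: success 98.6% versus 90.9%, a difference of 7.7 points. For the rounded counts 1/100 versus 9/100, Fisher's exact test gives p = 0.018. Power to detect this difference is about 69% (normal approximation) or 61% (Fisher, exact enumeration).
- Exited patients removed: 0 versus 0 failures, a difference of 0 by construction.
- If both rates were half as large: 0.7 versus 4.55 failures per 100, a difference of 3.85 points, likewise erased.

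**4. Direction for complications.** The documents give no complication rate, so this is illustrative only. Assume a 3% risk in successful insertions and k times that in failed ones, with the failure fractions f above. The rate in all attempts is 0.03 × (1 − f) + k × 0.03 × f.

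| k | Subclavian (f = 0.091) | Jugular (f = 0.014) | After removing exits |
|---|---|---|---|
| 1 | 3.0% | 3.0% | 3% vs 3% |
| 2 | 3.3% | 3.0% | 3% vs 3% |
| 5 | 4.1% | 3.2% | 3% vs 3% |
| 10 | 5.5% | 3.4% | 3% vs 3% |

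Removing exits distorts the rates only if failed attempts carry a higher risk (k above 1). In that case the loss favours the subclavian arm.

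**5. The success definition.**

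| Tip position | Objectives {7} | Outcomes {12} | Catheterisation protocol |
|---|---|---|---|
| Superior vena cava, not aligned | Not success | Success | Not acceptable |
| Right atrium, not upper part | Success | Success | Not listed |

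A non-aligned tip in the superior vena cava is a success in one section and a failure in another. If a correct location means one on the acceptable list, it may also be an exit. None of the three statements says that the catheter must lie in the allocated vein, so a catheter moved to another vein after a failed attempt could meet the tip wording.

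**The case against.** The strongest reply is that {11b} says what per protocol means in this trial: exclusion applies outcome by outcome. A failed insertion already has its success result and its immediate complications, and every patient has a chest x-ray. The list of analysis exclusions is headed for the CT and ultrasound outcomes only. Reasons for exit will be collected and reported, differences between arms in non-completion will be reported, and all patients are assessed for adverse events. Failures would therefore be visible. Analysis sets for secondary outcomes are also often left to the statistical analysis plan.

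Much of this stands. A reader might infer that the success comparison is bound to come out as 100% versus 100%. The documents do not support that as a certainty: it needs exit to remove data already collected, against a coherent reading of {11b}. Even on the literal reading, a tip misplaced on the first film and then corrected could count as non-success without an exit. A reader might also infer that complications concentrate in failed attempts; no figure in the documents shows this. The 1.4% and 9.1% are background misplacement rates, not rates of inability to place or correct a catheter.

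The reply does not remove the conflict. The exit list is separate from the outcome-limited exclusion list and carries no such limit. If {11b} already kept exited patients for results known at insertion, the sentence keeping the insertion questionnaire would be unnecessary. Listing exit reasons is not the planned between-group comparison. The point is also not that an analysis set is missing, but that the stated rules give different ones.

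The 7-day condition on the carrying questionnaire might look like a further defect. It is an explicit choice that matches the hypothesis of at least 7 days' use, and this point does not rest on it.

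**Conclusion.** The concern holds as a conflict between stated rules. The exit criteria coincide with failure of a named secondary outcome, and the protocol does not settle whether exited patients count for success rate or mechanical complications. On the literal reading, about 1 jugular and 9 subclavian failures per 100 would be erased, a difference of 7.7 points. On the outcome-specific reading nothing is lost. The size assumes that the background misplacement rates carry over as failure rates and that about 100 patients per arm are included; real-time ultrasound guidance may make the true rates lower. Any bias in complications depends on an unknown excess risk in failed attempts.

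The mismatch between the success definitions in Objectives {7} and Outcomes {12} does not depend on how exit is read. The primary CT outcome and its sample size are unaffected.

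**What to change.** 1. State that success rate and mechanical complications are analysed in all randomised patients with an attempted insertion, by allocated vein. Failed placement in the allocated vein or an incorrect tip location counts as non-success, and complications count from the first puncture.
2. State that exit ends follow-up for the CT and ultrasound outcomes but does not remove insertion data. Keep the per-protocol set for those two outcomes.
3. Reconcile Objectives {7}, Outcomes {12} and the Catheterisation protocol into one success definition. Which tip locations qualify is for the investigators to decide.
4. Optionally, report the carrying questionnaire for all patients who carried the allocated catheter, as a sensitivity analysis beside the planned set of 7 days or more.

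The cost is a wording change, made before the data are analysed and handled through the protocol's own amendment route. No new procedure is needed: the x-ray is done in every patient and adverse events are assessed in all. It is worth checking that the eCRF is completed for abandoned attempts.

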### Reasons for exclusion from primary outcome analyses as well as the secondary outcome concerning ultrasound examination

The patient is unable to perform a follow-up CT venography. Reasons for this include, but is not limited toaAn estimated glomerular filtration rate < 15 ml/min without ongoing dialysis treatment at the time for the CT scanbThe patient dies before follow-upThe tCDC is in situ for < 7 daysAn additional central venous catheter is placed in the right-sided subclavian or internal jugular vein before the follow-up CT. Vein punctures without catheterisation are accepted (e.g. for myocardial biopsies after heart transplant surgery)

Reasons for exit from the trial and for exclusion in any of the analyses will be collected and reported. Data from the questionnaire about discomfort and pain during the catheterisation procedure will be used regardless and the questionnaire about discomfort and pain during the use of the tCDC will be used if the tCDC has been in situ for ≥ 7 days.

### Strategies to improve adherence to interventions {11c}

Given the nature of the intervention, no specific strategy is planned to improve adherence of the intervention.

### Relevant concomitant care permitted or prohibited during the trial {11d}

Restrictions are applied if additional central venous catheters are needed before the CT venography has been performed at 1.5–3 months after tCDC removal. Additional central venous catheters may not be placed in any of the study veins but rather in the left subclavian vein, the left internal jugular vein or in a femoral vein. To prevent protocol violations, the restriction will be clearly documented in the medical charts and patients will be informed about this.

### Provisions for post-trial care {30}

Provisions for post-trial care are not applicable.

### Outcomes {12}

The primary outcome is the incidence of post-catheterisation CVS, defined as venous diameter reduction > 50% anywhere from the estimated insertion site to the tip of the catheter, detected by a CT venography performed 1.5–3 months after removal of the tCDC.

The CT venography will be performed according to a protocol designed for this trial (Attachment 1) with the purpose to keep the amount of intravenous contrast and radiation as low as possible (with a limit of 100 kV the amount of intravenous contrast is reduced by 30% and less radiation is needed by repositioning the shoulders in an arm holder).

The secondary outcomes are:To compare the performance of a focused ultrasound examination of the central veins to detect CVS with a CT venography (golden standard) with a threshold ofa50% venous diameter reduction, as this is the commonly used definition of CVSb80% venous diameter reduction, as it has been suggested that the severity of central veno-occlusive disease must reach a diameter reduction around 80% before upstream changes in blood flow are detectable by current Doppler techniquesTo compare the patients’ experience of discomfort and pain between the groups both during the catheterisation and when carrying the catheter by means of a questionnaire (Additional files 1 and 2)To compare catheter blood flow during dialysis and reported catheter-related dialysis dysfunction between the groups. A questionnaire to address this will be filled out by the dialysis nurse after every treatment, including both objective and subjective measures (Additional file 3)To compare the catheterisation success rate (defined as catheter tip placement in the superior vena cava or in the right atrium) between the two groupsTo compare the number of mechanical complications (defined as arterial puncture/catheterisation and pneumothorax) between the groups

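### Catheterisation success is defined in two conflicting ways, does not require the randomised vein, and its failures are also reasons to exit a per-protocol trial

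*Protocol article*

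**What the plan says.** Three places in the protocol article describe where the catheter tip should lie.

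- Objectives: success is "defined as catheter tip placement in the right atrium or in the superior vena cava with the catheter aligned with the vessel", judged on the chest x-ray after the procedure.
- Outcomes {12}: success is "defined as catheter tip placement in the superior vena cava or in the right atrium". Alignment is not mentioned.
- Catheterisation protocol: "Acceptable catheter tip locations are in the upper right atrium, at the cavo-atrial junction", or the SVC with alignment. This is a standard for the procedure, not an outcome definition. The x-ray is done in every patient.

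Four other places decide who is analysed.

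- Reasons to exit the trial lists failure to use the randomised vein, in which case "the catheter may then be placed in any vein at the discretion of the operator", and failure to achieve a correct tip position.
- Section {11b}, on discontinuing or modifying allocated interventions, sets a per-protocol analysis in which "patients that do not complete the follow-up for a specific outcome will not be included in the analyses of that outcome".
- Statistical methods {20a} repeats the per-protocol basis for all randomised patients.
- The section on exclusions from the primary outcome keeps the insertion-pain questionnaire whatever happens. It says nothing about the success outcome.

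**The concern.** A success rate that compares two routes needs a single definition, a link to the route, and a denominator that includes the failures. All three are in doubt here.

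The two definitions disagree on alignment, so the same x-ray can be scored either way. Neither asks whether the catheter went in through the allocated vein. The two procedural exit reasons are the events that make a catheterisation fail, so under a per-protocol analysis the failures may be removed before the rate is calculated.

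The Background gives misplacement as one of two reasons why the jugular route is currently recommended (1.4% against 9.1% for the right subclavian vein). The success outcome is where the trial would show whether that disadvantage persists. If failures leave the denominator, it cannot show this.

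**Working it through.** **Plan's own figure.** The protocol gives no power or sample size for catheterisation success. Its only calculation is for the primary outcome: 10% in both groups, margin 15 points, one-sided 5%, 80% power. n = (1.645 + 0.842)² × 2 × 0.10 × 0.90 / 0.15² = 49.5, that is 50 per group, as stated. Nothing below alters it.

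**Definitions side by side.**

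| Finding | Objectives | Outcomes {12} | Catheterisation protocol |
|---|---|---|---|
| SVC tip, aligned | success | success | acceptable |
| SVC tip, not aligned | failure | success | not acceptable |
| Right atrium, below the upper part | success | success | not listed |
| Good tip through a vein other than the randomised one | meets the wording | meets the wording | vein not addressed |

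The second row is a direct contradiction between two definitions of one outcome. The third is a difference between a procedural standard and an outcome. It matters because the exit rule refers to a correct tip position, and the procedural standard is the only list of acceptable positions.

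**How exited patients might count.** Three readings are open.

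1. Kept as failures. The x-ray is done in every patient, so follow-up for this outcome is arguably complete. No sentence says so.
2. Dropped. They have exited, and the analysis is per protocol.
3. Kept and scored on tip position alone. A rescue catheter with a good tip then meets the definition literally.

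**Size, subclavian arm.** Inputs:
- Tip failure 9.1%, the Background's misplacement figure. Treating misplacement as tip failure is an assumption, since the cited study's definition is not given.
- Share f in whom the randomised vein cannot be used. The protocol does not give it, so 0 to 10% is assumed.
- Tip success of a rescue catheter 98.6% (100 − 1.4, the Background's jugular figure), assumed.

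Formulas:
- Failures counted: (1 − f) × 0.909
- Rescue counted as success: (1 − f) × 0.909 + f × 0.986
- Vein-failure exits dropped, tip failures kept: 0.909
- Both kinds of exit dropped: 1, provided the exit rule uses the Catheterisation protocol's positions

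| f | Failures counted | Rescue counted | Vein exits dropped | Both exits dropped |
|---|---|---|---|---|
| 0% | 90.9% | 90.9% | 90.9% | 100% |
| 5% | 86.4% | 91.3% | 90.9% | 100% |
| 10% | 81.8% | 91.7% | 90.9% | 100% |

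At f = 10%, counting rescue catheters adds 91.7 − 81.8 = 9.9 points, and dropping all exits adds 100 − 81.8 = 18.2 points. The Background's gap between routes is 9.1 − 1.4 = 7.7 points.

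**Effect on the comparison.** With f = 0 in both arms and failures counted, the arms are 98.6% and 90.9%, a difference of 7.7 points. With both kinds of exit dropped they are 100% and 100%, a difference of 0, whatever the true failure rates are.

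**The case against.** The strongest reply has four parts.

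First, the Outcomes section may only abbreviate a definition that the Objectives section gives in full and the Catheterisation protocol supports. That may be how the difference arose. But both sections define the same outcome expressly, nothing says which prevails, and the Data Availability section describes the article as the full protocol.

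Second, the Catheterisation protocol is an operating standard and may be narrower than the outcome. This stands: its restriction to the upper atrium is not in itself a conflict of outcome definitions. It needs reconciling only because the exit rule depends on a correct tip position.

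Third, exits and their reasons will be collected and reported, and the Sample size section promises to report important differences between groups in non-completion. This also stands, so failures would not be hidden. They would appear as exits, however, and not in the outcome meant to measure them.

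Fourth, the Discussion says that the right-sided technique allows real-time ultrasound guidance of the guidewire tip, so the historical 9.1% may not carry over. That is fair. The percentages above illustrate the size of the problem and do not forecast the result.

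A reader might infer more: that the plan will credit rescue catheters to the allocated route, or that omitting alignment favours the subclavian arm. The documents support neither. A patient whose randomised vein cannot be used exits the trial, so under the per-protocol rule removal is likelier than being scored a success. Nothing in the protocol says how often malalignment occurs by either route, so no direction of bias can be claimed from it.

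**Conclusion.** The point holds for a secondary outcome. The Objectives and Outcomes sections contradict each other on alignment, and neither ties success to the randomised vein. Both follow from the text without any assumption.

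The protocol also makes the two kinds of procedural failure exit reasons and leaves their handling in this outcome unstated. The likelier consequence is a rate pushed towards 100% in both arms. Scoring a rescue catheter as a success is possible only on a literal reading. With up to 10% vein failure, the choice of handling moves the subclavian rate by up to about 18 points. That figure rests on the assumed vein-failure share and on treating historical misplacement as tip failure. Even with no vein failures, dropping tip-location exits removes the whole 7.7-point historical gap.

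The primary outcome, its margin and its sample size are not touched.

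**What to change.** Three changes of wording, made before analysis:

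1. Use one definition of success in the Objectives and Outcomes sections. The sponsor should reconcile alignment and the atrial tip location with the Catheterisation protocol, and state which positions count as correct for the exit rule. Which positions are right is a clinical decision for the sponsor.
2. Add that success requires placement through the randomised vein.
3. State that success is analysed in all randomised patients with an insertion attempt. Exits because the randomised vein could not be used, or because a correct tip location was not achieved, count as failures of the allocated route. These patients may still leave the other analyses.

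No new procedure is needed: the x-ray is already planned for every patient, and exit reasons are already to be collected. The cost is that the reported success rates may be lower.
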